## Abstract

**Background:**

To improve psychological treatments for major depressive disorder (MDD), a better understanding on how symptoms ameliorate during treatment is essential. In cognitive behavioral therapy (CBT), it is unclear whether procedures focused on the acquisition of CBT skills play a causal role in the improvement of CBT skills. In this randomized trial, we isolate a single CBT Skill Acquisition Procedure (CBTSAP) and test its direct effects on CBT skills and related therapy processes (i.e., change in (idiosyncratic) dysfunctional thinking and reward processing). We hypothesize that the CBTSAP causes improvements in CBT skills and related therapy processes compared to an active control condition. In addition, we hypothesize that individual differences in attentional bias and memory functioning (defined as learning capacity) moderate the effects of CBTSAP on outcomes and that using mental imagery as a cognitive support strategy to strengthen the effects of the CBTSAP will be most beneficial for patients with low learning capacity.

**Method:**

150 patients with MDD will be randomized to one of three conditions: 1. an active control condition, 2. CBTSAP, 2. CBTSAP plus mental imagery, all consisting of three sessions. Primary outcomes will be change in CBT skills, changes in (idiosyncratic) dysfunctional thoughts and behaviors, reward processing. Depressive symptoms are a secondary outcome. Measures of learning capacity will be conducted at baseline and tested as a potential moderator.

**Discussion:**

Knowing whether and for whom the acquisition of CBT skills leads to change in therapy processes and a subsequent reduction of depressive symptoms will inform on how to personalize and optimize psychotherapy outcomes for depression.

**Trial registration:**

The trial is registered at the German Clinical Trial Register (DKTR; registration number: DRKS00024116).

## Background

Current psychological treatments for depression are only effective for half of the patients (Cuijpers et al., 2021). Response to psychological treatments is limited and relapse rates are high (Steinert et al., 2014; Verduijn et al., 2017; Vittengl et al., 2007). To improve and innovate psychological treatments, a better understanding of how symptoms improve during treatment is essential.

Psychotherapies aim to reduce depressive symptoms by mobilizing therapy processes that seem central to the development and maintenance of depressive symptoms. Therapy processes can be defined as the mechanisms inside the mind of the patient that are activated by the therapeutic procedures delivered by the therapist with the intent of producing change (Bruijniks et al., 2018). In cognitive behavioral therapy (CBT; Beck et al., 1979), one of the most investigated treatments for depression, therapeutic procedures focus on three major therapy processes: dysfunctional thinking, behavioral activation and the acquisition of CBT skills (Barber & DeRubeis, 1989; Lorenzo-Luaces et al., 2016). First, cognitive change procedures aim to change the process of dysfunctional thinking (Garratt et al., 2007). Dysfunctional thoughts can be organized into different levels, some thoughts seem to occur more on a superficial level (negative automatic thoughts), while other thoughts are derived from more deeply integrated dysfunctional mental representations, that can include ﻿rules, expectations, or assumptions (attitudes) and sometimes even originate from early experiences in the childhood (schemas) (Dozois & Beck, 2008). Second, CBT includes procedures aimed at behavioral activation in order to improve deficits in reward processing (Dimidjian et al., 2011), such as a reduced response to reward or an oversensitive response to negative feedback (Chiu & Deldin, 2007; Eshel & Roiser, 2010; Smoski et al., 2009). The third therapy process, the acquisition of CBT skills, is related to both dysfunctional thinking and behavioral activation. CBT skills are defined as the ability to re-evaluate the accuracy of one's own dysfunctional beliefs (CT skills) and in this way change patterns of dysfunctional thinking and the ability to engage proactively in pleasurable activities as a way to target reward experience (BT skills) (Strunk et al., 2007).

The acquisition of CBT skills is maybe one of the most promising therapy processes of CBT for depression. In contrast to the procedures focused on cognitive change and behavioral activation, CBT skill acquisition is a therapy process that emphasizes the patients' ability to use these cognitive change and behavioral activation procedures themselves, outside the therapy sessions. In addition, successful use of CBT skills may protect the patient from developing new future episodes after successful treatments (Strunk et al., 2007). Research shows that after successful treatment, impairments such as dysfunctional mental representations (Arntz, 2020; Sheppard & Teasdale, 2004), negative processing of information (Elgersma et al., 2019; Spinhoven et al., 2018; Woody et al., 2017) or blunted reward processing (Dichter et al., 2012; Pechtel et al., 2013) may remain, thereby possibly increasing the risk of new depressive episodes. The acquisition of CBT skills might be essential to transfer learned content from the therapy session to daily life and to cope with dysfunctional therapy processes or symptoms in future scenarios outside the therapeutic context.

However, although multiple studies have pointed out that the acquisition of CBT skills is associated with reduced depression (Adler et al., 2015; Forand et al., 2018; Strunk et al., 2014; Webb et al., 2019) and seems specific to CBT (Bruijniks et al., 2022), it is still unknown whether CBT skill acquisition directly causes a reduction of symptoms of depression. In order to test the causal effects of a certain therapeutic procedure, it is necessary to isolate the procedure and investigate its direct effects on the hypothesized changes in therapy processes and outcome (Bruijniks et al., 2018). Two preliminary experiments that focused on the acquisition of CT skills already evaluated how a procedure focused on the acquisition of CT skills could be isolated (Bruijniks et al., 2018) and showed that a short cognitive skill acquisition procedure in the form of a group masterclass led to better CT skill acquisition compared to an active control procedure in a sample of distressed students (Bruijniks, Los, & Huibers 2020). A next step towards the clinical application of this finding would be to evaluate how a procedure focused on CBT skill acquisition causally affects the acquisition of CBT skills and subsequent symptom reduction in a clinically depressed sample.

Nevertheless, skill acquisition seems to be a multifaceted process that requires different cognitive and neurobiological resources (Anderson et al., 2016, 2018; Basak et al., 2011; VanLehn, 1996), which may be impaired in depressed patients. Compared to healthy individuals, depressed individuals have biased attention towards negative rather than positive information (Fu et al., 2008; Liu et al., 2012; Marchetti et al., 2018; Roiser et al., 2012) and suffer from a variety of deficits related to executive functioning, such as inhibition, planning and working memory (Snyder, 2013). Recent studies supported the hypothesis that individual differences in cognitive or neurobiological impairments may interfere with the success of psychological treatments. In a systematic review, cognitive and neurobiological impairments showed to be associated with impairments in dysfunctional thinking and reward processing while depressed patients with better cognitive control, but more emotional bias, before start of CBT seemed to benefit more from CBT’s procedures (Bruijniks, DeRubeis, et al., 2019). Possibly, patients who show more emotional bias are better able to tolerate and therefore target emotions as part of the CBT (Stange et al., 2017) while individuals with better cognitive capacities are more capable of integrating and implementing new information that was retrieved in the therapy session. CBT might help individuals with increased emotional bias, but limited cognitive capacity, to regain (emotional) control (Siegle et al., 2006). A recent experiment supports this suggestion, as results indicated that in healthy participants who received a stress induction, executive control under stress, but not under non-stressful circumstances, predicted the ability to reappraise negative material to become less negative (Quinn & Joormann, 2020). Investigating whether individual differences in cognitive or neurobiological impairments are associated with the success of a CBT skill acquisition procedure will provide insight in for whom CBT skill acquisition procedures will be more or less effective.

If individual differences in cognitive or neurobiological impairments are related to the success of CBT skill acquisition, this also means that the success of CBT skill acquisition might be improved by increasing the patients' capacity to learn from these procedures. One way to address and improve cognitive and neurobiological processes during treatment is by providing cognitive support. Examples are the use of memory strategies within sessions of CBT (Harvey et al., 2014, 2017) or providing short retrieval tests between the sessions (Bruijniks, Sijbrandij, et al., 2020). The major hypothesis is that by enhancing recall for the session content, the success of psychotherapy outcomes for depression can be improved and some studies provided preliminary evidence for this hypothesis (Dong, Lee, et al., 2017). However, to improve psychotherapy it might not only be important to improve recall of the session content but also improve and develop the therapy process. Yet, while current cognitive support strategies such as retrieval of newly learned information may improve recall of the session content, it might not be enough to improve CBT skill acquisition. According to theories on skill acquisition, the process of skill acquisition starts with learning new information (this can also be seen as the 'declarative' part of skill acquisition), but then repeated practice is necessary to turn it into a more procedural form in which the newly learned skill becomes more and more automatized over time (Anderson et al., 2018; Tenison & Anderson, 2016; VanLehn, 1996). To increase skill acquisition, it might therefore be necessary to use a strategy that supports both the declarative and procedural parts of memory.

One strategy that seems promising in affecting both declarative and procedural memory is mental imagery. Mental imagery refers to perceptual experiences in the absence of sensory input and constitutes a non-verbal way of information processing, closely related to the experience of emotions (Holmes & Mathews, 2010). Mental imagery allows us to simulate past and future experiences and because of this allows us to “try-out” different courses of actions and their emotional consequences (Ji et al., 2016; Moulton & Kosslyn, 2009). Given these properties of mental imagery, when applied to CBT skills, imagery could be used to simulate skill application (Renner et al., 2021). Mental imagery has been linked to improved acquisition of skills in non-clinical settings, such as tennis performance or the development of surgical skills (Anton et al., 2017; Dana & Gozalzadeh, 2017; Gregg et al., 2011; Kim et al., 2017; Kraeutner et al., 2016), but also to increased BT skills in a clinically depressed population (Renner et al., 2017). Additionally, mental imagery has been related to the improvement of cognitive functioning, such as recall of memories (Dalgleish et al., 2013) and prospective memory (i.e., memorizing to execute a previously formed intention at some point in the future; McFarland & Glisky, 2012; McFarland & Vasterling, 2018). We suggest that simulating applying CBT skills using mental imagery might be a potential efficient way to increase skill acquisition during psychotherapy (Renner et al., 2021).

The aims of this randomized trial are two-fold. The first aim is to investigate and compare the direct effects of three procedures (active control, CBT skill acquisition (CBTSAP), CBTSAP + mental imagery) on changes in therapy processes (the acquisition of CBT skills, changes in idiosyncratic dysfunctional thoughts and behaviors, general dysfunctional thinking and reward processing) and depressive symptoms in a sample of patients with a diagnosis of major depressive disorder who do not currently receive other psychological treatment. We expect that compared to an active control procedure, the procedures focused on CBT skill acquisition (CBTSAP and CBTSAP + mental imagery) will lead to more improvement in the therapy processes and depressive symptoms. Second, we will investigate whether the effect of the therapeutic procedures is moderated by individual differences in learning capacity. Learning capacity will be defined as the presence of memory functioning and emotional bias (i.e., where more emotional bias and better memory functioning are defined as better learning capacity). Following earlier literature on the measurement of memory (Unsworth, 2010; Wilhelm et al., 2013), the measurement of memory functioning will be composed of both working memory and long-term memory tasks. We expect that, compared to the active control procedure, better learning capacity will be associated with larger improvements in the therapy processes and depressive symptoms in both the CBTSAP’s. In addition, we expect a difference between CBTSAP with versus without mental imagery: patients with low learning capacity will have most benefit from mental imagery and lower learning capacity will therefore be associated with more improvement in the therapy processes and depressive symptoms in the CBTSAP with mental imagery compared to the CBTSAP without mental imagery condition.

Besides the two main aims of the study, additional secondary analyses will be conducted. Because earlier studies suggested that cognitive support might improve the effects of therapy by increasing memory of the session content (Dong, Lee, et al., 2017), we additionally included a measure of session recall in the study and will test whether session recall will differ between the procedures. Hypotheses of these secondary analyses are in line with our hypotheses for the main study aims: we expect session recall to be larger in the CBTSAP with mental imagery compared to the CBTSAP without mental imagery. In further secondary analyses we will investigate whether the effect of the procedures on depressive symptoms is mediated through one of the therapy processes and/or session recall and whether these mediation effects are specific to the CBTSAP's (compared to the active control procedure).

A conceptual model for the proposed study can be found in Figure 1.

**Figure 1 f1:**
[figure not shown]
Conceptual Model for the Proposed Study

## Method

### Design

Between-subject experimental design with three parallel conditions, each having an equal length of 3 x 45-minute sessions: 1) Active control procedure (*n* = 50), 2) CBT skill acquisition procedure (CBTSAP) (*n* = 50), 3) CBTSAP with mental imagery (*n* = 50). The Ethic Committee of Freiburg University approved the study (registration number: 20-1022) and the trial is pre-registered at the German Clinical Trial Register (DKTR; registration number: DRKS00024116).

### Participants

We aim to include 150 patients with a primary diagnosis of a major depressive disorder (MDD) (excluding non-dysthymic persistent major depressive disorder) as indicated by Structural Clinical Interview for DSM-5 Disorders (SCID-5-CV) and a score on Beck’s Depression Inventory II (BDI-II) ≥ 14 to ensure sufficient symptom severity. Patients should be aged between 18-65 and have sufficient knowledge of the German language (because therapy sessions will be held in German). To prevent any potential interference with the therapeutic procedures and/or measurement of learning capacity, patients with the presence of a previously stated diagnosis of attention-deficit/hyperactivity disorder or attention-deficit disorder, current drug or alcohol use disorder according to the Structural Clinical Interview for DSM-5 (SCID-5-CV) or a cluster A or B personality disorder known by admission to the treatment center are excluded. To ensure the effects are attributable to the current therapeutic procedures, patients who receive currently (other) psychological treatment or have received CBT focusing on a major depressive disorder in the previous year are excluded. To reduce risk of adverse events, patient who show a high risk of suicide according to the intake staff or a score > 1 on BDI_II item 13 (Suicidal thought or wishes) will be excluded.

### Sample Size

Based on a medium effect size, alpha = .05, power =.80, number of experimental conditions = 3, number of repeated measurements = 2 to 4 (G*power (Faul et al., 2007)), a total sample size of 102 to 120 participants would be needed to detect a main effect, and 42 to 57 participants to detect an interaction in a repeated measures ANOVA. Simulation studies suggest 80 to 100 participants to detect an interaction effect between three groups (Shieh, 2019) while simulation studies on multilevel analyses suggest *n* = 80 participants to detect a medium effect size with power =.80 (Aarts et al., 2014). Taking into account 20% drop-out, we aim to include a total of 150 participants.

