### Data Analyses

All statistical tests will be two-tailed (significance level alpha .05). Descriptives (means, standard deviations) for all measures will be provided for each condition. All analyses will be intention-to-treat and missing data will not be imputed.

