#### Main Analyses

The main analyses will be conducted in Stata. First, to test the direct effects of the different procedures on change in therapy processes and symptoms, differences on the primary and secondary outcomes between conditions (CBTSAP versus active control; CBTSAP versus CBTSAP + mental imagery; active control versus CBTSAP + mental imagery) will be tested using multilevel analysis with maximum likelihood estimation (measurements [Level 1] nested within patients [Level 2] nested within therapists [Level 3]). Because the WOR is only measured at two time points, differences between conditions on the WOR will be tested using a repeated measures ANOVA.

Second, to test whether the effect of the procedures is moderated by individual differences in learning capacity, learning capacity will be added as a moderator in the model. Moderation will be tested by adding learning capacity as a main factor and the interaction between learning capacity and condition to the multilevel regression model. For the WOR, the interaction will be added to the repeated measures ANOVA. Moderation of learning capacity will be tested separately for memory functioning and emotional bias. Memory functioning will be tested separately for each component of memory functioning (i.e., verbal working memory, visual working memory, long-term memory), while controlling for type I error (*p* < .016).

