This study is also the first that elaborately assesses learning capacity at baseline to investigate the moderating role of learning capacity on the effects of isolated CBT procedures. Earlier studies have indicated that depressed patients with more emotional bias and more memory functioning might show better improvement during CBT (Bruijniks, DeRubeis, et al., 2019), but these studies mostly investigated the role of learning capacity on the complete treatment package (i.e., a full CBT that includes multiple CBT procedures), primarily used neurobiological measures or where conducted in an elderly depressed population. The present study will be able to inform on the specific role of learning capacity in a key therapeutic procedure, the acquisition of CBT skills, in CBT for depression. In addition, a better understanding of the role of learning capacity and a CBT skill acquisition procedure on CBT outcomes might open up new avenues for future research on the role of skill acquisition and learning capacity in psychotherapy for depression in general. Another strength of the study is the repeated measurement of therapy processes, which will allow us to investigate how learning capacity affects the hypothesized mechanisms underlying the success of a CBT skill acquisition procedure and also how the CBTSAP might lead to reduction of depressive symptoms through these mechanisms. A final strength of the present study is that it includes a multimodal assessment, using not only self-report instruments but also a CBT skill test, idiosyncratic measures of therapy process change, behavioral tasks and eye-tracking. A limitation of the present study is that it is powered to find medium to large effects and will be underpowered to find small effects between the three treatment conditions.

In conclusion, while there are a number of effective evidenced based treatments for depression, many patients do not improve in treatment and progress in treatment innovation has been slow. One way forward is to isolate specific therapeutic procedures and test their direct effects on therapy processes and outcomes. Based on this experimental research framework we will conduct a randomized clinical study testing the direct effects of a key CBT procedure, CBT-skills, with or without a cognitive support strategy compared to an active control condition. The results of this study will contribute to a better understanding of individual differences in the effects of key CBT procedures.

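### The sample-size figures are for omnibus tests, not the three pairwise contrasts in change, so the claim of power for medium effects between conditions is unsupported, above all for the WOR

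*Protocol article*

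**What the plan says.** Sample Size sets the inputs as "Based on a medium effect size, alpha = .05, power =.80, number of experimental conditions = 3", with "number of repeated measurements = 2 to 4". It gives neither a number for the medium effect nor a correlation between measurements. Its result, for a repeated measures ANOVA, is that "102 to 120 participants would be needed to detect a main effect, and 42 to 57 participants to detect an interaction". It also cites simulation studies suggesting 80 to 100 participants for an interaction between three groups and 80 for a medium effect in multilevel analysis. Allowing for 20% drop-out, the target is 150, or 50 per arm.

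The aims, in Background, are about change: "the procedures focused on CBT skill acquisition (CBTSAP and CBTSAP + mental imagery) will lead to more improvement" than the active control. Main Analyses tests the conditions pairwise, "CBTSAP versus active control; CBTSAP versus CBTSAP + mental imagery; active control versus CBTSAP + mental imagery", in a multilevel model. The WOR has only two time points and is analysed by repeated measures ANOVA. Data Analyses fixes two-tailed tests at alpha .05. No power is stated for any pairwise contrast, yet the Discussion says of the study that "it is powered to find medium to large effects and will be underpowered to find small effects between the three treatment conditions".

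**The concern.** The figure that drives N belongs to a test that does not address the hypotheses. A between-condition main effect averages each patient's scores over all occasions. Randomisation follows the baseline measurement and the introduction session, so the expected difference between arms at those points is zero, and averaging them in dilutes any treatment effect. A condition-by-time interaction is the right kind of test for change. The stated interaction figure, however, is omnibus and small enough to suggest a very large effect on the change scale.

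What is at stake is the reading of null results. CBTSAP versus CBTSAP + mental imagery compares two active arms. If the Discussion sentence is taken at face value, a non-significant result there would be read as evidence against a medium difference, although the chance of detecting one may be well below 80%.

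**Working it through.** **Inputs.** From the protocol: three groups, 1:1:1; two-sided alpha 0.05; power 0.80; 2 to 4 measurements (m); 20% drop-out, so 150 × 0.8 = 120 completers, 40 per arm. Assumed, because not stated: medium means f = 0.25 for the ANOVA tests and d = 0.5 for a pairwise contrast; equal correlation ρ between occasions; no therapist clustering.

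**1. The main-effect figure.** Noncentral F with λ = f²Nm / (1 + (m − 1)ρ), df 2 and N − 3. At f = 0.25 and ρ = 0.5:
- m = 2: N = 120 (λ = 0.0625 × 120 × 2 / 1.5 = 10.0)
- m = 3: N = 108
- m = 4: N = 102 (λ = 0.0625 × 102 × 4 / 2.5 = 10.2)

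This is exactly 102 to 120, and 120 / 0.8 = 150. The protocol's figures therefore imply ρ = 0.5.

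**2. What that test detects.** Suppose f = 0.25 exists at the post measurement and the baseline difference is zero. Averaged over two occasions the effect halves to f = 0.125. With 120 completers λ = 0.015625 × 120 × 2 / 1.5 = 2.5, and power is about 27%.

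**3. The interaction figure.** λ = f²Nm / (1 − ρ), df 2(m − 1) and (N − 3)(m − 1). At f = 0.25 and ρ = 0.5, N = 42 (m = 2), 36 (m = 3), 30 (m = 4). The 42 reproduces. At m = 2, λ = 0.0625 × N × 2 / 0.5 = 0.25N, which is a one-way analysis of change scores with f² = 0.25, that is f = 0.5. It corresponds to a largest between-arm difference in change of 1.06 to 1.22 SD. With f = 0.25 on the change score itself, λ = 0.0625N: 159 completers are needed, and 120 give 68%.

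The 57 needs an unstated setting. With ρ about 0.32 the formula gives 57 (m = 2) and 42 (m = 4). With ρ = 0.5, m = 3 and a sphericity correction of 0.5 it also gives 57. At ρ = 0.32 the formula in step 1 gives 105 (m = 2) to 81 (m = 4), so that one value does not yield both stated ranges.

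**4. Pairwise contrast, one pre and one post score (the WOR).** Noncentral t, 40 per arm, noncentrality (0.5 / √v) × √(40/2) = 2.236 / √v. For a change score v = 2(1 − ρ); baseline-adjusted, v = 1 − ρ².

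| ρ | change | baseline-adjusted |
|---|---|---|
| 0.3 | 46% | 64% |
| 0.5 | 60% | 72% |
| 0.7 | 81% | 87% |

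Power crosses 80% at ρ about 0.69 (change) or 0.62 (adjusted). The repeated measures ANOVA planned for the WOR corresponds to the change column. At ρ = 0.5 the detectable d at 80% power is about 0.63, or 0.63 × √0.75 = 0.55 adjusted.

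**5. Pairwise contrast, outcomes measured more often** (40 per arm, d = 0.5, ρ = 0.5).
- Effect building linearly to d = 0.5 at the last occasion, tested as a slope over 3, 4, 5 or 6 occasions: 60%, 64%, 69%, 74%.
- Constant effect, one pre and two post scores (CCL, RPI, TEPS): v = 0.75 for mean change, 0.50 adjusted; power 72% and 88%.
- Constant effect, two pre and four post scores (BADS-SF, CCSC): v = 0.375 and 0.292; power 95% and 98%.

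**The case against.** The strongest reply is that nothing in Sample Size is miscalculated. That stands: 102, 120, 42 and 150 are right for the tests they describe, and 57 is reachable, though only at a setting the article does not give. A reader might infer an arithmetic error; the documents do not support that.

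Second, the shortfall is conditional. Neither ρ nor a numerical effect size is stated, and at ρ = 0.7 even the WOR contrast has 81% to 87%. Reading medium as f = 0.25 rather than d = 0.5 also helps: with three arms it implies a largest pairwise difference of about 0.53 to 0.61, and 77% to 88% power for that contrast with one baseline-adjusted post score at ρ = 0.5. This stands as a limit on the claim. But the protocol's own 102 to 120 points to ρ = 0.5, and the WOR analysis is not described as baseline-adjusted.

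Third, the 60% belongs to the one-pre, one-post layout, which among the primary outcomes only the WOR has. That stands too. A constant effect from the first post-randomisation score is optimistic, though, and a gradual effect leaves these outcomes below 80% at ρ = 0.5.

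Fourth, the cited simulation results may bear on the planned multilevel model. They are not at hand, so their fit can be neither relied on nor dismissed. Finally, the Discussion already concedes low power, but only for small effects.

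**Conclusion.** The point holds in limited form. No stated figure gives power for the pairwise contrasts in change, and the figure that sets N is for an effect that includes the pre-randomisation baseline. At the ρ = 0.5 implied by the protocol's own numbers, with 40 completers per arm and d = 0.5, power on the WOR is about 60% as planned, or about 72% baseline-adjusted. Other outcomes range from 60–74% (effect building linearly) to 72–98% (constant effect). The Discussion's statement about medium effects is therefore not supported, in particular for the WOR.

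A reader might go further and conclude that the trial is underpowered outright, or that every contrast has about 60% power. The documents do not support either: the result turns on an unstated ρ, the numerical reading of medium, the number of occasions and the model.

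**What to change.** Keep N = 150 and change the text:
- In Sample Size, stop presenting the main-effect and interaction figures as the power for the planned comparisons.
- State power, or the minimal detectable d, for each pairwise contrast by type of outcome, with the assumed d, ρ, number of occasions and model. For the WOR at ρ = 0.5 and 40 per arm, the detectable d is about 0.63, or 0.55 if baseline-adjusted.
- State the ρ and any other settings behind 42 to 57.
- In the Discussion, qualify the word medium to match, naming the WOR.

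The cost is rewording, and a less favourable power statement for some outcomes; no extra patients are needed. A pooled contrast of both CBTSAP arms against control could be added, but it is optional: two of the three planned contrasts already address that hypothesis, and pooling would not correct the sample-size text.
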